**Figure 1 figure1:**
[figure not shown]
A flowchart of enrollment and data collection for the ProAct trial.

### Intervention

#### Immediate Intervention Group

The intervention consists of 4 web-based sessions hosted through a videoconferencing platform (Zoom Inc) and facilitated by 1 or 2 members of the research team. The 4 sessions will be delivered in weeks 1, 3, 5, and 8 of the program. Summaries of each session, including the target constructs and behavior change techniques used in each session, are presented in Table 1. The first session will involve only parents and will last 90 minutes. It focuses on instructing parents in the use of autonomy-supporting parenting behaviors. The remaining 3 sessions will involve both parents and children and will last 45 minutes. Session 2 prompts a discussion of the benefits of an active lifestyle, including enjoyment and importance, and gets participants to set individual and joint physical activity-related goals. Session 3 teaches participants how to make action plans and coping plans (ie, problem-solving) when pursuing physical activity goals. Session 4 covers social norms related to physical activity, has participants specify their identity related to physical activity, and prompts social support strategies within each dyad.

**Table 1 table1:** Content and targets for each intervention session in the ProAct trial. Behavior change techniques preceded by an “M” are drawn from the Motivation and Behavior Change Techniques [38]. Behavior change techniques preceded by a “T” are drawn from the Behavior Change Taxonomy version 1 [39].

Session	Target constructs	Behavior change techniques
Session 1: 90 minutes and parents only	Autonomy supportive parenting	M3. Use non-controlling, informational language M5. Provide a meaningful rationale M6. Provide choice M7. Encourage the person to experiment and self-initiate the behavior M10. Show unconditional regard M12. Use empathic listening M16. Clarify expectations T1.1 Goal setting yeah T1.4 Action planning T4.1 Instruction on how to perform the behavior T4.2 Information about antecedents T5.3 Information about social and environmental consequences T5.6 Information about emotional consequences T8.1 Behavioral practice/rehearsal T16.3 Vicarious consequences
Session 2: 45 minutes, parents, and children	Attitude	M4. Explore life aspirations and values M6. Provide choice M7. Encourage the person to experiment and self-initiate the behavior M16. Clarify expectations M17. Assist in setting optimal challenge M19 Help develop a clear and concrete plan of action M20 Promote self-monitoring T1.1 Goal Setting (behavior) T1.3. Goal Setting (outcome) T1.5 Review behavior goal(s) T1.6 Discrepancy between current behavior and goal T2.3 Prompt self-monitoring of behavior T4.1 Instruction on how to perform the behavior T5.6 Information about emotional consequences T15.3 Focus on past success
Session 3: 45 minutes, parents, and children	Perceived behavioral control and self-regulation	M15. Address obstacles for change M19. Help develop a clear and concrete plan of action M20. Promote self-monitoring M21. Explore ways of dealing with pressure T1.2 Problem-solving T1.5 Review behavioral goals T1.6. Discrepancy between current behavior and goal T2.2 Feedback on behavior T8.7 Graded Tasks T15.1 Verbal persuasion about capability T15.3 Focus on past success.
Session 4: 45 minutes, parents, and children	Subjective Norm and perceived autonomy support	M2 Prompt identification of sources of pressure for behavior change M8. Acknowledge and respect perspectives and feelings M9. Encourage asking of questions M14. Prompt identification and seek available social support T1.1 Goal Setting (behavior) T1.3 Goal Setting (outcome) T1.4 Action planning T1.5 Review behavioral goals T1.7 Review Outcome Goals T3.2 Social Support (Practical) T3.3 Social Support (Emotional) T6.2 Social comparison T6.3 Information on others’ approval. T13.1 Identification of self as role model T13.5 Identity associated with changed behavior

In addition to the web-based sessions, participants will have access to a website that includes materials that support the content of each session. This includes worksheets, slide decks and recorded versions of the sessions, a menu of physical activities suitable for parents and children, and further practice materials.

Between sessions, participants will receive SMS text messages that ask them to provide written feedback on their progress; offer advice, suggestions, or reminders; or prompt reflection on their motives for physical activity. Parent participants will also be granted access to a moderated web-based chat forum (WhatsApp group [Meta Facebook, Inc]) in which parents can share their experiences with the sessions and provide and receive social support from other participating parents. Intervention materials are available on the internet [40].

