#### Waitlist Control Group

Participants assigned to the waitlist control group will complete the same data collection procedures as the immediate intervention group but will not be required to undertake any alternative intervention tasks during the data collection period. After the data collection period, participants in the waitlist control group will be invited to receive the intervention and accompanying materials.

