## Results

The project team received final notification of research funding approval for the current project from the Finnish Ministry of Education and Culture, Sport Science Funds, in March 2022 (PROJECT 350904), and the trial has been preregistered on ClinicalTrials.gov (ID 806/13.00.04.00/2023). Enrollment into the trial commenced on September 20, 2023. Enrollment is scheduled to continue until March 2024, with the final collection of follow-up data scheduled for December 2024.

We expect that the research will provide valuable formative evidence for the efficacy of a theory-driven family-based physical activity intervention strategy. Further, as the proposed trial includes open materials and tests of the theory-driven mechanistic effects that may encourage behavior change, this research may also serve as a valuable stepping stone to the development of more large-scale, low-cost interventions for family behavior change.

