This study tests a theory-based family behavioral intervention aimed at promoting change in physical activity participation in parent-child dyads. The intervention aims to foster autonomous motivation, enhance social support, and reduce perceived barriers to exercise in an atmosphere that is accepting and open. The intervention will make a unique contribution to practice and theory. Given the low levels of physical activity participation in adult and child populations, demonstrating the efficacy of web-based behavioral intervention in increasing physical activity that is both replicable and potentially scalable will make a valuable contribution to practice in health care contexts. In this research, we aim to enhance the potential usefulness of this intervention in the context of informing refined, scalable interventions based on results with the use of open materials and data, including intervention content and delivery guides. Further, from a scientific perspective, the application of a theory-based intervention developed in line with current practice intervention guidelines presents a potentially valuable test of mechanistic effects presented in the integrated behavior change theory and its component models [12-15], identifying the “active ingredients” of the intervention that are associated with desired outcomes. That is, while the integrated behavior change theory has been supported in several correlational studies [22,23,52], such research only provides an indication of the likely variables most important in determining behavior and can by their correlational nature not be used for any assertions of direction or causality. Thus, a key contribution of this intervention is assessing not only whether the program is successful in changing behavior, but also in assessing which target constructs mediate the effects of the intervention on behavior change and may therefore be most valuable when refining current strategies or developing new programs.

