### Limitations

Beyond the expected value presented by the research, it is also important to note that the trial faces some expected and inherent challenges and limitations. For example, as the intervention does not include any reward or payment to participants beyond the benefits of the intervention itself, it is likely that parents who consent to enroll themselves and their child in the program will already be at least somewhat motivated to change their physical activity behavior. Such an issue has been noted in the previous parent-for-child interventions [53]. If this is the case, it is likely that the intervention effects will not be as strong as expected, as already motivated participants possess a lesser degree of potential for change than might be expected in families with unmotivated parents. While this nonetheless poses a challenge to the intervention, it is important to note that motivation or knowledge of the need for physical activity is commonplace [9,54], even as actual activity levels remain low. As the strategies used in this intervention include training parents in autonomy support rather than controlling strategies that may inhibit their child’s autonomy and thus harm the development of active lifestyles [20,55], as well as strategies to bridge the intention-behavior gap, this trial still has bona fide value in targeting this key population. However, the problem of accessing and enrolling unmotivated families into intervention programs remains a concern for behavior change research.

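### Intervention materials are described as openly available online while waitlist controls are still being followed, so controls could reach part of the programme, and the article describes no access limit or exposure check

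*Protocol article*

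**What the plan says.** **Availability.** The Immediate Intervention Group section says "Intervention materials are available on the internet [40". The Outcomes overview cites the same reference for the full questionnaires. Results says that "as the proposed trial includes open materials and tests of the theory-driven mechanistic effects", and Potential Findings and Implications describes refining the intervention "with the use of open materials and data, including intervention content and delivery guides".

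**Participant website.** The Immediate Intervention Group section also describes a website for participants: "This includes worksheets, slide decks and recorded versions of the sessions, a menu of physical activities suitable for parents and children, and further practice materials". The article does not say whether this is the same place as reference 40.

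**Control condition.** Under Waitlist Control Group, controls "will not be required to undertake any alternative intervention tasks during the data collection period". The section continues: "After the data collection period, participants in the waitlist control group will be invited to receive the intervention and accompanying materials". Trial Design and Study Procedures likewise place the intervention for controls after all outcome data are in.

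**Timing.** According to Results, enrolment opened on 20 September 2023. "Enrollment is scheduled to continue until March 2024, with the final collection of follow-up data scheduled for December 2024".

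**Motivation.** Limitations considers it likely that consenting parents "will already be at least somewhat motivated to change their physical activity behavior".

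**Stopping rule.** Study Procedures cancels the 6-month data collection if the intervention shows no effect on leisure-time physical activity at 3 months.

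**The concern.** The comparison depends on controls going without the programme until their last outcome is recorded. The article sets that condition, yet describes the programme's materials as already reachable online while enrolment is still under way and follow-up is to come. The trial is web-based from recruitment to delivery, and a waitlist design tells control parents that a programme exists and that they must wait for it. Some may look for it.

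Use of the materials by controls would raise their activity and the psychological constructs that the programme targets. Under intention-to-treat this biases the primary and secondary contrasts toward no effect. It also weakens the path from intervention to mediator in the mediation model. A diluted 3-month contrast could lead to cancellation of the 6-month follow-up, which would lose the test of persistence. Data Analysis includes nothing on control exposure, the only programme-related survey items described (under Acceptability) go to the intervention arm, and the sample size allows for attrition alone.

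**Working it through.** **1. The passages side by side.**

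| Point | Where | What it implies |
|---|---|---|
| Intervention materials online, present tense, no embargo or login mentioned | Immediate Intervention Group | Reachable at the time of writing |
| Enrolment still scheduled to continue to March 2024 | Results | That time falls within the trial |
| Materials open, including content and delivery guides | Results; Potential Findings and Implications | Public access is intended |
| Accompanying materials for controls after data collection | Waitlist Control Group | Controls should be unexposed until then |
| Last follow-up December 2024 | Results | The period of possible exposure covers both follow-ups |

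That control parents know their allocation is not stated; it follows from the waitlist design.

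**2. The plan's own figures.** Power Analysis averages 0.45 and 0.48: (0.45 + 0.48)/2 = 0.465, or f = 0.465/2 = 0.2325. The article uses f = 0.235 (d = 0.47), a small difference with no bearing here. With noncentrality N × f², α = 0.05 and power 0.80:

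- numerator df = 2 gives N = 178, the stated figure (power 0.801);
- numerator df = 1, a plain two-arm contrast, gives N = 145;
- 178/0.7 = 254.3, matching the stated 254.

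Neither 178 nor 254 includes an allowance for exposed controls.

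**3. Dilution.** Let q be the share of controls who use the materials and h the share of the effect that they gain. The documents give neither value, so both are assumptions. The loss of contrast is L = q × h, and the diluted effect is d × (1 − L).

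- q = 0.05, h = 0.5: L = 0.025; 0.465 × 0.975 = 0.453.
- q = 0.20, h = 0.5: L = 0.10; 0.465 × 0.90 = 0.419.
- q = 0.20, h = 1.0: L = 0.20; 0.465 × 0.80 = 0.372. This is an outer limit only, because files alone do not supply the live sessions, text messages or chat group.

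**4. Power at N = 178**, using f = 0.235 × (1 − L) and counting participants as independent, which is the basis on which 178 reproduces:

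| L | Power, df = 2 | Power, df = 1 |
|---|---|---|
| 0 | 0.80 | 0.88 |
| 0.025 | 0.78 | 0.86 |
| 0.10 | 0.71 | 0.80 |
| 0.20 (outer limit) | 0.60 | 0.70 |

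**5. Stopping rule.** The article does not define how no effect will be judged. If it means a non-significant 3-month test, and the assumed effect is real, the chance of cancelling the 6-month follow-up is 1 − power. At L = 0.10 it rises from 0.20 to 0.29 (df = 2) or from 0.12 to 0.20 (df = 1). At L = 0.025 it rises by about 0.02 in either case.

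**The case against.** The strongest reply is that the case for open access rests on a citation whose target is not shown. The same reference serves the questionnaires, so it may be a research repository meant for readers, and its language, completeness, access settings and release date are unknown. The recorded sessions and worksheets are placed on the participant website, which may be somewhere else. This stands: a reader might infer that recorded sessions are public, and the documents do not support that.

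The sections also do not strictly contradict each other. One schedules delivery to controls; the other says where materials can be found. That stands as well, but they pull against each other, and the article does not resolve how both are to hold during follow-up.

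Third, a condensed article need not list a contamination question or repository settings, and the full surveys are held elsewhere. It therefore cannot be said that exposure would go undetected, only that the article describes no check. The point does not rest on that silence: the article affirmatively describes public availability of something that controls are meant to go without.

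Fourth, the motivation statement is hedged and concerns changing activity, not searching for files. Nothing says that families joined because they wanted this programme, and recruitment includes a panel company. Controls who never look for the materials are quite possible.

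Finally, the bias runs toward no effect, so it would not manufacture a false claim of benefit. This is true, but a missed effect and a cancelled follow-up are also costs.

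**Conclusion.** The point holds as a cheap improvement. The article describes intervention materials as openly available during a period in which the control arm is meant to be without them, and describes neither an access limit nor an exposure measure. What this shows is that controls could reach part of the programme. A reader might infer that controls will be contaminated, or could gain the whole effect from the online files; the text supports neither.

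The size is unknown. With 5-20% of controls gaining about half of the effect, the contrast shrinks by 2.5-10% (d from 0.465 to about 0.45-0.42). Power at 178 then falls from 0.80 to 0.78-0.71 on the calculation that reproduces the plan, or from 0.88 to 0.86-0.80 for a two-arm contrast. The low end is trivial and the high end is noticeable. A 20% loss is an implausible upper bound. These figures rest on assumed uptake and benefit, and on independent participants.

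**What to change.** Keep the public copy of the intervention content under embargo until the last 6-month outcome has been collected, and give the intervention arm access through the participant website only. The questionnaires can stay public. If reference 40 is already restricted, one sentence saying so settles this part.

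Add one item to the 3- and 6-month surveys in both arms asking whether the family saw or used programme materials. Name a sensitivity analysis of the primary outcome that uses the control-arm answers, with intention-to-treat kept as the main analysis. The item is worth having even if an embargo comes too late, because it makes any dilution measurable.

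The cost is a repository setting, one survey item and one additional analysis. The downside is that open release of the materials, a stated aim of the project, is delayed to the end of follow-up.

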#### Waitlist Control Group

Participants assigned to the waitlist control group will complete the same data collection procedures as the immediate intervention group but will not be required to undertake any alternative intervention tasks during the data collection period. After the data collection period, participants in the waitlist control group will be invited to receive the intervention and accompanying materials.

### Outcomes

#### Overview

Measures of psychological constructs will be assessed using multi-item scaled survey measures, while leisure-time physical activity is to be assessed using self-reported surveys and observationally through accelerometer measurements. All items were translated into Finnish by native speakers and piloted on a sample of 8- to 12-year-old Finnish children and their parents. Full measures are available on the internet [40].

#### Primary Outcomes (Physical Activity and Sedentary Time)

Self-reported physical activity and time spent in sedentary activities for both parents and children will be assessed using the Godin-Shepard leisure time exercise questionnaire [41], where participants will be required to report the number of occasions they engaged in light, moderate, and vigorous physical activity for 15 minutes or longer. Sedentary time will be measured using 2 items per participant, targeting weekdays and weekend days separately (eg, “In the past 7 days, how much time did you spend sitting during a typical weekday after school or weekend day?”) [42]. Items are scored on a sliding scale from “no time” upwards in increments of half an hour.

#### Secondary Outcomes

##### Device-Measured Physical Activity

Physical activity will also be assessed using a hip-worn triaxial accelerometer (Hookie AM20; Traxmeet Ltd). Each dyad will be mailed 2 accelerometers, detailed instructions on wearing the device, and a diary for recording when they wore the accelerometer, how they commuted to school or work, and any events that may have inhibited accurate data (eg, missed days and exercise done without the device). Raw data from accelerometers will be processed using the *GGIR* package in R software (R Foundation for Statistical Computing) [43], with outcome scores provided as the amount of time spent engaged in sedentary behavior, light physical activity, moderate physical activity, and vigorous physical activity.

##### Autonomy-Supportive Parenting

Autonomy-supportive parenting practices will be assessed using a 4-item questionnaire based on measures used in a previous study [44], with responses provided on 5-point scales (1=strongly disagree to 5=strongly agree).

##### Perceived Autonomy Support

Perceived autonomy support will be assessed using the perceived autonomy support scale for exercise settings [45]. For children, the scale refers to autonomy support from parents, while for parents, the scale makes reference to autonomy support received from family. All items are scored on a 5-point Likert scale (1=strongly disagree to 5=strongly agree).

##### Autonomous and Controlled Motivation

Autonomous and controlled motivation for both parents and children is assessed using 4 items each [46], with responses provided on 5-point scales (1=strongly disagree to 5=strongly agree).

##### Attitude

Attitude toward engaging in physical activity is assessed using 3 items with a common stem [44,47], with responses provided on a 5-point semantic differential scale (eg, unenjoyable [1] to enjoyable [5]).

##### Subjective Norms

Subjective norms in parents are assessed using 3 items referring to important others [44,47]. Children answered similar items, but in specific reference to family and friends separately. All items are scored on a 5-point Likert scale (1=strongly disagree to 5=strongly agree).

##### Perceived Behavioral Control

Perceived behavioral control is assessed in both parents and children using 2 items [44,47], with responses provided on 5-point scales (1=strongly disagree to 5=strongly agree).

##### Intention

Intention to engage in leisure time physical activity is assessed in both parents and children through 3 items [44,47], with responses provided on 5-point scales (1=strongly disagree to 5=strongly agree).

##### Self-Monitoring

Self-monitoring toward physical activity is assessed using 2 items [44,48], each scored on a 5-point Likert scale (1=strongly disagree to 5=strongly agree).

##### Habit

Habits are assessed using the 4-item automaticity subscale of the self-reported habit index [49,50], with responses provided on 5-point scales (1=strongly disagree to 5=strongly agree).

##### Acceptability

For participants in the immediate intervention group, the postintervention (3 months) web-based questionnaire will include survey items assessing the accessibility and feasibility of intervention procedures. Participants will also be invited to attend a 45-minute web-based exit interview to explore participant perceptions of the intervention content and possible improvements for future implementation.

